### Medical Monitoring (see Table 1 for Schedule of Events)

The baseline medical assessment will include a physical examination, monitoring of side effects/symptoms (utilizing the side-effect checklist), completion of the Acquired Involuntary Movement Scale (AIMS) to monitor extrapyramidal symptoms, taking of vital signs (temperature plus lying and standing heart rate and blood pressure), an EKG, bone mineral density, and comprehensive lab work (see Table 1). An EKG will be repeated at Weeks 2, 4, and 15. At each clinic visit, a urine sample (urinalysis and pregnancy test) will be taken, vital signs completed, and weight recorded.

The AIMS and an adverse event checklist are also completed at each clinic visit.

#### Primary Outcome Measures

The primary outcome measure will be the change from baseline on the total score of the EAT-26 score measured at week 12 prior to topping off the medication, and BMI change over the first 12 weeks of treatment.

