### Sample Size

Given the relative novelty of this application of olanzapine, no formal evaluation of the drug has yet been conducted on youth, making it difficult to accurately estimate sample size requirements. However, after consultation within our clinical team we believe that a decrease of 5 points on the EAT-26 scale would be clinically meaningful. The following assumptions were therefore used for sample size calculations: i) a minimal clinical important difference of 5 on the EAT-26 score; ii) an estimated standard deviation of 7.07; iii) two-sided test; iv) a power of 80% and a type I error of 5%; v) a provision for one interim analysis according to the O'Brien and Fleming criteria [35]. With these assumptions, the total sample size necessary is 64 participants. Anticipating a drop-out rate of at most 2.5%, the formula of Donner [36] may be used to adjust the sample size assuming an intention to treat analysis. The resulting total sample size is thus 67 participants (33 and 34 participants per treatment group). We anticipate that this study will take two years to complete enrollment.

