### Statistical Analysis

Descriptive summaries of demographic and treatment balance will be generated with respect to all participant characteristics at baseline. Dichotomous variables will be summarized using percentages, normally distributed continuous variables will be summarized using means together with standard deviations, and continuous variables that are not normally distributed will be summarized using medians together with range.

Statistical analysis of the data will follow the intention-to-treat principle for the main analysis of treatment outcomes. For participants who develop clinical events that will lead to withdrawal from the study, or that are lost to follow-up prior to the 12-week primary endpoint, we will use the BMI plus last value captured for the EAT-26 test as a method of imputation of missing data.

A student's t-test (assuming a normal distribution of the measures; otherwise, Wilcoxon Mann-Whitney test will be used) will be used in order to compute the change between the EAT-26 and the difference in BMI from baseline to week 12. If necessary, a linear regression model will be fit to assess treatment effect adjusting for variables thought to influence outcome that could result in imbalance between treatment groups at baseline. Treatment effect and its 95% confidence interval will be generated for each primary outcome.

To examine secondary outcomes, the differences between study groups will be assessed using Student's t-tests (as described above for primary outcome). In order to avoid multiple testing issues, results will be compared with an alpha value adjusted for the number of tests performed using the Bonferonni criterion.

Although the study is not powered to detect differences in safety, we will nevertheless compare the frequency of adverse events between the two study groups using chi-square or Fisher's exact test.

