### Interim analysis

One interim analysis will be run after the enrolment of the 33^rd ^patient, which will be representative of half of the sample. This analysis will focus on the primary outcome and safety issues. Using the O'Brien-Fleming criteria for two-sided test, the alpha-level of this interim analysis will be 0.005. The final analysis will be conducted using an alpha-level of 0.048.

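### Two primary outcomes share one undivided pair of alpha levels with no decision rule, while the stated 5% error and 80% power are derived for EAT-26 alone

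*Protocol article*

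**What the plan says.** All references are to the protocol article; no separate SAP is at hand.

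- **Primary Outcome Measures** joins two quantities: the change in "EAT-26 score measured at week 12 prior to topping off the medication, and BMI change over the first 12 weeks of treatment".
- **Statistical Analysis** specifies a t-test (or Wilcoxon test) "in order to compute the change between the EAT-26 and the difference in BMI from baseline to week 12", and adds: "Treatment effect and its 95% confidence interval will be generated for each primary outcome".
- **Statistical Analysis**, next paragraph, opens "To examine secondary outcomes, the differences between study groups will be assessed using Student's t-tests" and ends with the only multiplicity correction in the article: "results will be compared with an alpha value adjusted for the number of tests performed using the Bonferonni criterion".
- **Interim analysis** sets one interim level, 0.005, and one final level: "The final analysis will be conducted using an alpha-level of 0.048". Neither is divided between EAT-26 and BMI.
- **Sample Size** rests on "a minimal clinical important difference of 5 on the EAT-26 score", a standard deviation of 7.07, and "a power of 80% and a type I error of 5" per cent. It gives no effect size or standard deviation for BMI.

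No section says whether success needs one outcome or both, or gives an order of testing.

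**The concern.** An error rate and a power belong to a decision rule. The article states 5% and 80% for a single test of EAT-26, yet declares two primary outcomes. Whether those figures describe the trial depends on a rule it does not give.

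A split result is the practical problem. The Background cites weight gain with this class of drug, so BMI could be positive while EAT-26 is not, or the reverse. As written, the plan cannot say whether that is a positive trial, and the choice could be made after the data are seen. It is equally open which outcome could support stopping at the interim look.

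**Working it through.** **1. Reproduce the plan's own figure.** Inputs from Sample Size: difference 5, SD 7.07, two-sided 5%, power 80%.

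n per arm = 2 × [SD × (z₀.₉₇₅ + z₀.₈₀) / difference]² = 2 × [7.07 × (1.960 + 0.842) / 5]² = 31.4, so 32 per arm and 64 in total.

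An assumed O'Brien-Fleming inflation of 1.008 gives 31.6, still 32. For the stated 2.5% drop-out, 64 / 0.975² = 67.3, which matches 67. The calculation is sound for EAT-26 alone at the full 5%, so no alpha was reserved for BMI.

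**2. Either outcome suffices.** With two independent single-look tests at 0.05, the error is 1 − 0.95² = 9.75%. For the actual design, two-look z statistics were simulated (2,000,000 pairs, half the information at the interim as the article says, critical values 2.807 for p = 0.005 and 1.977 for p = 0.048):

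| Correlation of the two outcomes (assumed) | Overall type I error |
|---|---|
| 0 | 9.8% |
| 0.3 | 9.5% |
| 0.5 | 9.0% |
| 0.8 | 7.8% |

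Each outcome on its own comes out at about 5.0%, so the boundaries are right for one outcome.

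**3. Alpha split equally.** EAT-26 power at 32 per arm:

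| Level | t-test | Normal approximation |
|---|---|---|
| 0.05 | 79.5% | 80.8% |
| 0.048 | 79.0% | 80.3% |
| 0.025 | 70.2% | 72.2% |
| 0.024 | 69.6% | 71.6% |

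Splitting costs about 9 percentage points of EAT-26 power and needs no assumption about BMI. By the formula in step 1, 80% power at 0.025 needs 39 per arm, or 78 evaluable; 78 / 0.975² gives about 82 enrolled.

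**4. Both outcomes required.** The type I error stays at or below 5%. Joint power is the bivariate normal probability Φ₂(z_p1, z_p2; correlation), with EAT-26 power p1 = 80% and BMI power p2 assumed:

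| BMI power (assumed) | Correlation 0 | 0.3 | 0.5 | 0.8 |
|---|---|---|---|---|
| 80% | 64% | 67% | 69% | 73% |
| 90% | 72% | 74% | 75% | 78% |
| 95% | 76% | 77% | 78% | 79% |
| 99% | 79% | 80% | 80% | 80% |

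**The case against.** **The alpha for each outcome is not spelled out.** The primary-outcome paragraph names no level, and both Primary Outcome Measures and Interim analysis use the singular for the primary outcome. This stands. That each outcome gets the full 0.048 is an inference from a single undivided level and from Bonferroni being confined to the secondary outcomes. What the text supports is that no split is stated.

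**A reader might infer that the trial must have either 9 to 10% type I error or clearly less than 80% power.** The documents do not support that. The error reaches that range only if either outcome counts and the correlation is about 0.5 or lower. With both required, the power loss depends on a BMI power that cannot be computed from the article and could be negligible. A fixed sequence would avoid both problems for EAT-26.

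**The article condenses a longer plan.** Order of testing and the basis for interim stopping are often left to an SAP, and their absence alone would be no finding. But the article does more than stay silent: it fixes the alpha levels, places the multiplicity correction on the secondary outcomes, and states 5% and 80% from one of two declared primaries. That mismatch is in the text.

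**The power basis could be all 67 patients.** With 33 and 34 per arm, t-test power is 80.9% at 0.048 and 71.9% at 0.024. The loss is the same size; the figures above use the 64 that the plan says it needs.

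A reader might also set the 95% interval against the 0.048 test level. The multipliers are 1.960 and 1.977, a difference of about 1%, which is too small to matter and is not part of this point.

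**Conclusion.** The point holds in this form: two primary outcomes are declared and separately analysed, one undivided pair of alpha levels is given, and the stated 5% and 80% are established only for EAT-26. The size of the problem depends on the rule eventually applied:

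- **Either outcome:** about 8 to 10% type I error in place of 5%, for correlations from 0.8 down to 0 (assumed range).
- **Equal split:** about 70% EAT-26 power in place of 80%, at 32 per arm by t-test.
- **Both outcomes:** 64 to 73% joint power if BMI power is 80%, 72 to 78% if 90%, and about 79 to 80% if 99%, for correlations 0 to 0.8. BMI power is an assumption throughout.

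The sample size calculation is not itself wrong; it covers one of the two outcomes that the trial calls primary.

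**What to change.** State the decision rule in the protocol or SAP before the interim look. One workable rule is a fixed sequence:

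1. Test EAT-26 at week 12 at 0.005 (interim) and 0.048 (final).
2. Test BMI at the same levels, and only if EAT-26 is significant.
3. Assess interim efficacy on EAT-26 alone.
4. State that the 80% power applies to EAT-26.

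This is one paragraph and no extra patients. It keeps the 5% error and the planned EAT-26 power at the present sample size. The price is that BMI cannot be claimed as confirmatory if EAT-26 fails.

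Other rules would also settle the matter, at a cost. An equal alpha split needs about 78 evaluable patients in place of 64 to keep 80% power for EAT-26. Requiring both outcomes needs a stated BMI effect and SD; if BMI had the same standardised effect as EAT-26 (an assumption), 80% joint power would need 84 evaluable patients at correlation 0, falling to 74 at 0.8.

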#### Secondary Outcome Measures

Change from baseline in the EAT-26 score measured at week 6, 15 (i.e. off medication) and at the end of the maintenance period (week 40), as well as BMI change measured at the same time points will be analyzed as for the primary outcomes. Change from baseline in the CAPI, the CDI, the MASC, the EDS3 and the CBCLwill be calculated for weeks 6, 12, 15 and 40.

## Discussion

### Safety Issues

At each visit, the patient will be asked about any harm they may have experienced and clinical assessments will be performed to determine the safety of olanzapine. All adverse events will be recorded on the Case Report Form (CRF) and entered into the database. Harms include any untoward medical occurrence that a study participant experiences, whether or not that event is considered to be in relation to the study drug. Serious adverse events (SAE's) are those events that result in death or are life threatening, result in hospitalization or prolongation of hospitalization, result in persistent or significant disability, or result in a congenital birth defect. All SAE's will be reported to Health Canada as per the required reporting timelines. As well, all SAE's will be reported to an independent Data Safety and Monitoring Committee (DSMC).

If a patient endorses Item "9" "I want to kill myself" on the Child Depression Inventory (CDI), the project coordinator will immediately contact the Research Investigator and establish a plan to assess risk for suicide. The project coordinator will survey the item immediately after the adolescent completes the questionnaires.

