### Psychological Measures

Patients' psychological well-being will be measured utilizing the following six scales:

Eating disorder symptoms will be measured using the **Eating Attitudes Test **(EAT-26) [28], the EAT-26 is a 26-item self-report questionnaire with a 6-point scale that measures 3 domains of disordered eating: dieting, bulimia and food preoccupation, and oral control. The EAT-26 is a widely used, well-validated instrument in this clinical population. In this study, the total EAT-26 score will be used.

Psychiatric Symptoms will be measured using the **Children's Acuity of Psychiatric Illness Scale-Child and Adolescent **(CAPI) [29], The CAPI is an outcome measure for children and adolescents that is designed to monitor change deriving from contact with mental health services. The CAPI yields a total raw score and four subscale scores, including Risk Factors, Symptoms, Functioning, and Systems support. The scale has good inter-rater reliability (.78 to .85) and good internal consistency (.87) across a variety of settings [29].

Depressive symptoms will be measured using the **Children's Depression Inventory **(CDI) [30]. The CDI is a 27-item questionnaire, which asks respondents to endorse statements about themselves reflecting cognitive, behavioural and somatic symptoms of depression. Items are rated on a 3-point scale indicating symptom severity. Total scores on the CDI can range from 0 to 52, with higher scores indicating higher levels of depressive symptomatology. The measure has been shown to have acceptable internal consistency (alphas = .71 to .89) as well as good discriminant validity when classifying children with no significant psychopathology versus depressed children [30]. The total score of the CDI will be used in this study.

Anxiety symptoms will be measured using the **Multidimensional Anxiety Scale for Children **(MASC) [31]. The MASC is a 39-item 4-point Likert-style self-report which demonstrated a satisfactory to excellent range for the intraclass correlation coefficient for the three subscales: physical symptoms, harm avoidance, and social anxiety in a sample of youth (ICC = 0.79 to 0.92) [32]. The total score on the MASC will be used in this study.

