Clinicians will be asked to complete the **Eating Disorder Symptom Severity Scale **(EDS3) [33] which will examine their observations of the youth's eating disorder symptoms such as: dieting behaviours, body image preoccupations, agitation related to eating/body image, fear of fat, food anxiety, as well as overall motivation for treatment. Clinicians involved in the study have attended a workshop meant to improve inter-rater reliability for this scale (r = .75 to r = .80 was deemed acceptable)

Parents will be asked to complete the **Child Behavior Checklist **[34] in order to evaluate their perceptions of their child's mood and anxiety. The Child Behaviour Checklist (CBCL) has been demonstrated to be a reliable measure when completed by parents, with a mean alpha 0.80 being reported [34]. The CBCL is a widely used, well-validated instrument in pediatric populations.

The psychological measures will be completed at baseline, weeks 6, 12, 15 and 40 (see Table 1). The patient will complete the EAT, CDI and the MASC; the parent will complete the CBCL; and the treating physician and therapist will complete the CAPI and EDS3.

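### The suicide-risk trigger is worded as endorsement of one CDI Item 9 statement, so the other response above the lowest level has no stated action

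*Protocol article*

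**What the plan says.** The rule is in the Safety Issues section of the protocol article: "If a patient endorses Item '9' 'I want to kill myself' on the Child Depression Inventory (CDI), the project coordinator will immediately contact". That contact is with the research investigator, and the two set up a plan to assess the risk of suicide. The section adds: "The project coordinator will survey the item immediately after the adolescent completes the questionnaires". It therefore names who reads the item, when, what sets off the response and what the response is.

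The Psychological Measures section describes the instrument. The CDI "asks respondents to endorse statements about themselves reflecting cognitive, behavioural and somatic symptoms of depression". On the format it says: "Items are rated on a 3-point scale indicating symptom severity". The total score is read "with higher scores indicating higher levels of depressive symptomatology". On timing: "The psychological measures will be completed at baseline, weeks 6, 12, 15 and 40".

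Other safety provisions stand beside this rule. Safety Issues says: "At each visit, the patient will be asked about any harm they may have experienced". The CAPI, completed by the treating physician and therapist at the same time points as the CDI, yields "four subscale scores, including Risk Factors, Symptoms, Functioning, and Systems support". The Trial Design section keeps both groups on standard care, including psychological treatment.

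**The concern.** An item with three graded responses has two above the lowest level. The rule attaches an action to one quoted statement. The coordinator is required to look at the item at once, so an answer at the other raised level would be seen, but the article does not tell the coordinator what to do with it. The response would be left to individual discretion.

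The setting makes this worth correcting. Participants are girls aged 12 to 17, and the Background section lists depression and suicidality among the psychological consequences of anorexia nervosa. What is at stake is a prompt risk assessment for an adolescent whose answer staff have already read. The point does not touch sample size, type I error, power or the efficacy analysis.

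**Working it through.** The article gives no figure to reproduce. The check sets its statements side by side and counts.

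**1. What is endorsed.** Psychological Measures uses the verb for statements: the respondent endorses statements about herself. Safety Issues uses the same verb in front of one quoted first-person statement. The natural reading is that the trigger is that statement.

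**2. Responses without a stated action.**
- Levels per CDI item (Psychological Measures): 3.
- Levels with a stated action (Safety Issues): 1, the quoted statement.
- Lowest level, where no action would be expected: 1.
- Remainder: 3 − 1 − 1 = 1.

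The article does not print the three Item 9 options. That the quoted statement is the most severe is inferred from its content. The count needs less than that: whichever raised level the quoted statement occupies, the other raised level has no stated action.

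**3. Whether another section supplies the action.** None does. The harm enquiry at each visit, the CAPI Risk Factors subscale and standard care are not linked to an Item 9 answer, and none carries a stated suicide-risk escalation step.

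**4. How soon another scheduled study contact would follow.** Table 1 has weekly visits from week 0 to week 15 and then one at week 40.
- After a CDI at week 0, 6 or 12, the next study visit is 1 week later.
- After the CDI at week 15, the next study visit is 40 − 15 = 25 weeks later.
- After the CDI at week 40, no further study visit is scheduled.

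Week 15 is also the first CDI after study medication has stopped, since Table 1 shows a dose of 0 from week 14.

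**5. Ceiling on extra calls under a wider trigger.** At most one call arises per form.
- Scheduled forms: baseline and weeks 6, 12, 15 and 40, so 1 + 4 = 5.
- A footnote to Table 1 lets a CDI done at screening less than two weeks earlier stand in for week 0. If the screening form is more than two weeks old and is repeated, there are 5 + 1 = 6. This assumes that the rule is also applied to the screening form.

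The article gives no frequency of intermediate Item 9 responses. Neither the number of extra calls below this ceiling nor the amount of risk now left without a stated response can be estimated.

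**The case against.** The strongest case on the other side has four parts.

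*The words may name the item.* The grammatical object in the rule is the item, and the following sentence has the coordinator look at the item, not at a statement. The quoted words could be a label for the suicide item, so that any raised answer counts as endorsing it. This reading is possible and cannot be excluded. It is the less natural one given how the article uses the verb for the CDI. If it is what the sponsor meant, the sentence does not make that clear to the coordinator, and the same clarification serves.

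*A journal article condenses.* The full protocol may hold a broader suicide-risk procedure, and its absence here would not be a fault. That stands, and it limits the point. The article is not silent, however: it publishes a specific trigger, and the point concerns how that trigger is worded.

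*The threshold is a judgement.* The wording of the middle response is not shown, and a lower trigger brings assessments for some participants at low risk. This is fair: the documents do not show how much risk a middle answer carries. The case for the wider trigger rests on the severity grading, the population and the small cost, not on a measured benefit.

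*Other cover is substantial.* It includes psychiatric assessment at entry, weekly visits to week 15, continuing psychological care, the clinician-completed CAPI and an independent safety committee. These may well pick up risk by another route, and this part largely stands. It does not close the gap, because none is tied to the answer, and the weekly contact ends at week 15.

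A reader might go further and infer that intermediate answers will be ignored, or that the trial has no other protection against suicide risk. The article supports neither. It does not say that other responses prompt nothing, it does not bar the coordinator from raising them, and the safeguards above are real.

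**Conclusion.** The point holds as a narrowly worded trigger in a stated safety rule. Read as written, 1 of the 3 graded responses to Item 9 prompts contact, 1 is the lowest level, and 1 has no stated action. Other safeguards reduce the consequence without removing it, least of all after week 15.

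This rests on two assumptions: that the trigger is the quoted statement and not the whole item, and that the full protocol does not already set a wider one. Because both are open and missed risk cannot be quantified, confidence is medium. The change is recommended as an inexpensive improvement to participant safety. It is not evidence that participants would go unprotected.

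**What to change.** Add one sentence to Safety Issues: any Item 9 response above the lowest level leads the project coordinator to contact the investigator the same day for a suicide-risk assessment. Keep immediate contact for the quoted statement.

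The change needs that sentence and an instruction to the coordinator. No visit, measure or staff post is added, because the item is already read on completion. The downside is some extra same-day calls and risk assessments, some of them for participants at low risk, within the per-form ceiling worked out above.
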